##### **➤ OS**

The median OS will be estimated using the Kaplan-Meier method and presented with the Kaplan-Meier curve.

The comparison of OS between intervention arms will be performed using a stratified log-rank test. The HR and the corresponding 95%CI will also be provided based on a Cox proportional hazard model, using ECOG PS (0 vs. 1), brain metastases (yes vs. no), liver metastases (yes vs. no), and treatment after patient withdrawal (yes vs. no) as concomitant variables. The results of the unstratified log-rank test and results of the Cox proportional hazard model without covariates adjustment will also be provided.

Subgroup analysis of OS will be performed based on stratification factors.

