### **3.2 Participant Withdrawal, Removal, or Termination**

#### **3.2.1 Criteria for Participant Withdrawals**

- (1) The patients developed disease progression and could not benefit from further treatment determined by the investigators;
- (2) The patients experienced the AEs without tolerance and alleviation;
- (3) Subjects who experienced SAEs and were not suitable for further study;
- (4) Patients who did not meet the eligibility criteria following the additional review;
- (5) The serious protocol deviation or violation affected the evaluation of safety and efficacy;
- (6) Patients who withdrew consent;
- (7) Patients with failure to follow up for any reason.

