**Post-treatment Follow-ups**

All subjects will be followed up every 8 weeks (including telephone follow-up) to collect data on other antitumor therapy and disease status. The treatment regimens, cycles, and outcomes of any other treatment must be recorded during the trial. Post-treatment follow-up will be conducted until

death. Reasons and the date of death will be recorded for overall survival analysis.

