### **13.4 Efficacy Analysis**

#### **13.4.1 Analysis of Primary Efficacy Endpoints**

##### **➤ PFS**

The median PFS will be estimated using the Kaplan-Meier method and presented with the Kaplan-Meier curve.

The comparison of PFS between intervention arms will be performed using a stratified log-rank test. The HR and the corresponding 95%CI will also be provided based on a Cox proportional hazard model, using ECOG PS (0 vs. 1), brain metastases (yes vs. no), and liver metastases (yes vs. no) as concomitant variables. The results of the unstratified log-rank test and results of the Cox proportional hazard model without covariates adjustment will also be provided.

Subgroup analysis of PFS will be performed based on stratification factors.

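### The Cox model that supplies the OS hazard ratio adjusts for treatment received after withdrawal, so that hazard ratio does not estimate the effect as randomised

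*Protocol*

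**What the plan says.** Protocol section 13.4.1 treats the two primary endpoints almost alike.

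- **PFS.** The HR and 95% CI come from a Cox model "using ECOG PS (0 vs. 1), brain metastases (yes vs. no), and liver metastases (yes vs. no) as concomitant variables". These are the three stratification factors of section 4.3, all known at randomisation.
- **OS.** The hypothesis test is a log-rank test: "The comparison of OS between intervention arms will be performed using a stratified log-rank test". The HR and 95% CI come from a Cox model that has the same three factors and a fourth term: "and treatment after patient withdrawal (yes vs. no) as concomitant variables".
- **Also for OS.** An unstratified log-rank test is added, and "results of the Cox proportional hazard model without covariates adjustment will also be provided".

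Two other places show when the extra variable becomes known. Section 3.2.1 lists among the withdrawal criteria: "The patients developed disease progression and could not benefit from further treatment determined by the investigators". Section 7, on post-treatment follow-up, says: "All subjects will be followed up every 8 weeks (including telephone follow-up) to collect data on other antitumor therapy and disease status". Section 13.1 makes the ITT set, analysed as randomised, the primary set for efficacy.

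**The concern.** A covariate in the model for a randomised comparison should be fixed before treatment can influence it. Treatment after withdrawal is not, for three reasons.

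1. **Immortal time.** A patient must progress or stop for another reason, and then live long enough to start something else. Early deaths are all coded no. The yes group looks better even if the later therapy does nothing.
2. **Mediation.** Arm affects progression and toxicity, these affect withdrawal, and withdrawal opens the way to later therapy. Conditioning on later therapy removes part of the treatment effect, or adds to it.
3. **Unstable coding.** The no group mixes early deaths with patients still on study treatment. At the OS interim (70% of events) some patients coded no will become yes later.

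At stake is the effect size for a primary endpoint: the HR and interval that the protocol sets beside the stratified log-rank test, and from which readers judge the benefit.

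**Working it through.** **Inputs from the protocol.** Section 4.1.1: control medians of 10 months (OS) and 4 months (PFS), 12 months' accrual, 18 months' follow-up, 85% power, type I error 0.05. Section 13.2.2: the 0.05 is two-sided. Section 4.1.2: arm 1 versus control has PFS HR 0.6, OS HR 0.7, 284 OS events in 381 patients and 424 after dropout. Section 4.1.4: 738 patients randomised 1:1:1, so 246 per arm.

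**The plan's own OS figure.** Schoenfeld: 4(1.960 + 1.036)² / (ln 0.7)² = 282.3, rounded up to 283, against 284 stated. Exponential OS with the stated accrual and follow-up gives 283.6 events in 381 patients, and 381/0.90 = 424. The OS design reproduces and is not in question.

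**Assumptions, not in the protocol.** The variable means antitumour therapy started after study treatment and is entered as a fixed yes/no. Later therapy is possible only if the patient is alive 1 month after progression. Uptake among eligible patients is varied.

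**Model A.** 246 per arm, 400 trials per scenario. OS and PFS are exponential at the protocol's control medians, with PFS-OS correlation 0.6 (Gaussian copula). Later therapy has no effect on survival. Each Cox model is fitted with arm alone, then with arm plus the yes/no covariate.

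| True OS HR / PFS HR | Uptake, control/arm 1 | Share treated, control/arm 1 | HR without covariate | HR with covariate |
|---|---|---|---|---|
| 0.70 / 0.6 | 60% / 60% | 43% / 39% | 0.70 | 0.68 |
| | 70% / 50% | 50% / 32% | 0.70 | 0.62 |
| | 80% / 40% | 57% / 26% | 0.70 | 0.56 |
| | 50% / 70% | 36% / 46% | 0.70 | 0.73 |
| 1.00 / 0.6 | 60% / 60% | 43% / 33% | 1.00 | 0.95 |
| | 70% / 50% | 50% / 27% | 1.01 | 0.88 |
| | 80% / 40% | 57% / 22% | 1.00 | 0.78 |
| | 50% / 70% | 36% / 38% | 0.99 | 1.01 |
| 1.00 / 1.0 | 60% / 60% | 43% / 43% | 1.00 | 1.00 |
| | 70% / 50% | 50% / 36% | 1.01 | 0.92 |
| | 80% / 40% | 57% / 29% | 1.00 | 0.81 |
| | 50% / 70% | 36% / 50% | 1.00 | 1.10 |

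- Without the covariate the model returns the truth throughout.
- With it, the estimate is undisturbed only when arms and uptake are all equal. Equal uptake alone does not protect: with PFS HR 0.6 and no OS effect, 60%/60% reads 0.95, because fewer arm 1 patients progress in time to be treated. The trial is designed to produce such a PFS difference.
- In the eight scenarios with PFS HR 0.6, the inert therapy itself shows an HR of 0.55-0.63. That is the immortal-time artefact.

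**Model B.** A structural check with an illness-death model. Monthly hazards for progression, death without progression and death after progression are 0.156, 0.0173 and 0.104 in control, and 0.0936, 0.0104 and 0.101 in arm 1. Uptake is 0.40-0.65 and analysis is at 340 deaths in the two arms, which is a model choice and not a protocol figure. With an inert therapy, an HR of about 0.69-0.70 reads 0.66-0.69 over much of the range. The widest results were 0.63 (uptake 0.65 control, 0.40 arm 1) and 0.75 (0.40, 0.65). Identical arms with more later therapy in control read 0.92-0.96. The mechanism is the same, and the artefact is mostly smaller than in Model A.

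**The case against.** The strongest reply is that nothing confirmatory depends on this model, and that an HR without the covariate is already planned. Both parts are true.

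- **Testing.** A reader might infer that the OS tests or the type I error are compromised. The documents do not support that. Sections 13.2.3 and 13.4.1 test OS by stratified log-rank, with one-sided limits of 0.0074 (interim) and 0.0228 (final) within the fixed sequence. The Cox Wald test decides nothing, so a change in its rejection rate says nothing about trial success.
- **Only one HR.** A reader might infer that every reported OS HR is biased. The covariate-free Cox model gives a valid treatment-policy HR. What remains is that this model also drops the stratification factors, and that the contaminated model is named first, beside the stratified test. No OS counterpart to the PFS model is planned.
- **Direction.** A reader might infer that the adjusted HR flatters the experimental arm. It can, but with more later therapy in arm 1 the estimate moves the other way (0.73-0.75 for a true value near 0.70).
- **Working later therapy.** If later therapy reduces the hazard (HR 0.7), the adjusted and unadjusted HRs differ more: 0.63 against 0.75 at 70%/50% in Model A. That gap mixes bias with a change of estimand and should not all be counted as bias.

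It could also be said that the variable might be handled as time-dependent. The protocol does not say so, and the yes/no wording reads as fixed. A time-dependent version would remove the immortal time but would still adjust for a mediator.

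**Conclusion.** The point holds as a defect of the effect estimate, not of the test. The OS HR and 95% CI attached to the stratified log-rank test come from a model containing a post-randomisation, survival-dependent covariate, and do not estimate the as-randomised effect. The PFS model in the same section avoids this.

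For an inert later therapy, a true HR near 0.70 reads from 0.56 to 0.73-0.75 across the two models. Identical arms with moderately more later therapy in control read about 0.92-0.96, and 0.81 at the most extreme imbalance tried (80%/40%). These figures rest on the assumed uptake, the 1-month lag and the assumed link between progression and death. The protocol gives no rates of later therapy, so neither size nor direction can be fixed for this trial. That the estimate is not the randomised effect does not depend on those assumptions.

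**What to change.** In section 13.4.1, and in the SAP if it repeats the text:

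1. Delete treatment after withdrawal from the OS Cox model.
2. Take the OS HR and 95% CI from a Cox model stratified by, or adjusted for, ECOG PS, brain metastases and liver metastases, as for PFS. Keep the model without covariates as supportive.
3. Tabulate later antitumour therapy by arm, from data that the 8-weekly follow-up already collects.
4. If the influence of later therapy is of interest, put it in a labelled sensitivity analysis that states its estimand and uses a method suited to treatment switching.

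The cost is one deleted phrase and one table. Sample size, event targets, alpha limits and test order do not change.

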#### **13.4.2 Analysis of Secondary Efficacy Endpoints**

##### **➤ ORR**

The number and percentage of subjects with an objective response (PR or CR) will be presented. The ORR and corresponding 95%CI will be summarized using F-distribution by binomial probabilities. The difference in ORR between intervention arms will be compared by the stratified Cochran-Mantel-Haenszel (CMH) test. Stratification factors as items specified in section 4.3.

##### **➤ DOR**

The median DOR will be estimated using the Kaplan-Meier method and presented with the Kaplan-

Meier curve. The comparison of DOR between intervention arms will be performed using a stratified log-rank test. DOR will be only analyzed in responders.

➤ **DCR**

The number and percentage of subjects with the disease control (PR, CR, or SD) will be presented. The DCR and corresponding 95%CI will be summarized using F-distribution by binomial probabilities. The difference in DCR between intervention arms will be compared by the stratified CMH test. Stratification factors as items specified in section 4.3.

➤ **6-month and 12-month PFS rates**

The PFS rate and the corresponding 95%CI for each intervention arm will be estimated using the Kaplan-Meier method and compared with Fisher's Exact Test.

➤ **12-month and 18-month OS rates**

The OS rate and the corresponding 95%CI for each intervention arm will be estimated using the Kaplan-Meier method and compared with Fisher's Exact Test.

➤ **HRQOL**

HRQOL will be summarized by descriptive statistics. The changes of each item from baseline at each scheduled visit will be summarized by mean, SD, median, minimum, and maximum within each intervention arm. The grade of each item will be presented by the number and percentage and compared with the Wilcoxon rank sum test between intervention arms.

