#### B Progression-free Survival per Investigators per iRECIST

[figure not shown]

**Figure S2. Duration of response as assessed by blinded independent central review and investigator review (intention-to-treat population).**

Panel A shows the Kaplan–Meier curves for duration of response in patients who had a response assessed by blinded independent central review, and Panel B shows the Kaplan–Meier curves for duration of response in patients who had a response assessed by investigator review. This analysis included only patients who had an objective response as per RECIST 1.1. Duration of response was estimated with the Kaplan–Meier method and compared between treatment groups using the stratified log-rank test. Stratification factors included Eastern Cooperative Oncology Group performance status, brain metastases, and liver metastases. Hazard ratios and associated 95% two-sided confidence intervals were estimated by a Cox proportional hazards model. *P* values are two-sided. Tick marks indicate censored data. EC=Etoposide/carboplatin.

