### **Secondary objectives:**

- To compare the ORR, DCR, duration of response (DOR), 6-month PFS rate, 12-month PFS rate, 12-month OS rate, 18-month OS rate, and quality of life (QOL) across the three treatment arms.
- To compare safety and tolerability based on incidence and severity of AEs and serious adverse events (SAEs), as well as abnormal laboratory test indicators across the three treatment arms.
- To evaluate the immunogenicity of TQB2450 plus anlotinib and EC.

- To explore additional biomarkers related to efficacy, mechanisms of action, safety, and/or pathological mechanisms.

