#### **4.1.4 Determination of Total Sample Size**

Considering the sample size estimation in sections 4.1.2 and 4.1.3, 738 subjects will be finally enrolled in this trial and be randomly assigned (1:1:1) to three groups. The interim analysis and final analysis for PFS are conducted for this trial after 174 and 347 cases of the planned PFS events, respectively. The interim analysis and final analysis for OS are performed for this trial following 348 and 497 cases of the planned OS events, respectively.

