## 13. Statistical Analysis

### 13.1 Analysis Datasets

**Intention-to-treat (ITT) Analysis Set:** All randomized patients are included for efficacy analysis, according to the ITT principle. For the ITT population, patients will be considered in the treatment group as randomized.

ITT population is the primary analysis set and will be used for all efficacy and baseline characteristics analysis.

**Per-protocol Set (PPS):** All patients of the ITT population who receive the pre-defined minimum cycle of study treatment, had at least one imaging evaluation, without any major protocol deviation, with favorable compliance, and complete CRF.

PPS will be used for the per-protocol analysis of the primary efficacy variable and key secondary efficacy variables. The final PPS will be determined by the principal investigator, statisticians, and sponsors before the database lock.

**Safety Analysis Set (SS):** All randomized patients who receive at least one study treatment and have at least one safety assessment.

SS will be used for the safety analysis. For the SS population, patients will be considered in the treatment group as treated.

Baseline characteristics analysis will be performed for the ITT population. The analysis of the primary efficacy variable will be performed for the ITT and PPS population. The primary set for efficacy is the ITT. The analysis of laboratory data, AEs, and adverse reactions will be performed for the SS population.

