### (3) Type I error control for interim efficacy analysis based on OS

One interim analysis for OS is planned for this trial after 70% of the planned OS events (348 cases). If expected efficacy is observed, early declaration of the trial due to efficacy would be considered. The interim analysis will be conducted by iDMC.

Type I error will be controlled by the O'Brien-Fleming spending function approach. According to the O'Brien-Fleming spending function approach, in the interim efficacy analysis based on OS, the one-side significance level is set as  $\alpha_1 = 0.0074$  in the interim analysis and  $\alpha_2 = 0.0228$  in the final analysis.

- In the interim analysis:  $P_1 \leq \alpha_1$ , early declaration of the trial will be considered according to actual results;
- In the final analysis:  $P_2 \leq \alpha_2$ , the between-group difference in OS will be considered statistically significant.

$P_1$  = the one-side P value in the interim analysis;  $P_2$  = the one-side P value in the final analysis;

The tests sequence and type I error in the final analysis are shown in the following figure:

[figure not shown]

A two-sided test with a significance level of  $\alpha=0.05$  will be used for secondary efficacy endpoints and safety analysis. Two-sided  $P \leq 0.05$  will be considered statistically significant with a 95%CI.

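### The between-arm log-rank test of duration of response uses responders only, so it is not a randomised comparison and its P value cannot be read as a treatment effect on duration

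*Protocol*

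**What the plan says.** Four places in the Protocol bear on this.

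- **Section 13.4.2, DOR.** Medians and curves come from Kaplan-Meier. Then: "The comparison of DOR between intervention arms will be performed using a stratified log-rank test". The next sentence sets the population: "DOR will be only analyzed in responders". No hazard ratio for DOR is planned here.
- **Section 13.2.2 (3).** A two-sided test at 0.05 "will be used for secondary efficacy endpoints and safety analysis". DOR is a secondary endpoint, so its log-rank P value falls under this rule. No sentence calls it descriptive.
- **Section 2, secondary objectives.** The aim is "To compare the ORR, DCR, duration of response (DOR), 6-month PFS rate, 12-month PFS rate, 12-month OS rate, 18-month OS rate", together with quality of life, across the three arms.
- **Section 13.1.** "ITT population is the primary analysis set and will be used for all efficacy and baseline characteristics analysis".

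The supplementary results bound with the Protocol show the analysis carried out. The caption of Figure S2 says "This analysis included only patients who had an objective response as per RECIST 1.1" and describes log-rank P values and Cox hazard ratios, under a title that names the intention-to-treat population.

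**The concern.** Randomisation makes the arms comparable at baseline. It does not make the responders in one arm comparable with the responders in another. If a drug turns some non-responders into responders, its responder group gains patients who have no counterpart among control responders. Their durations may be shorter or longer than those of patients who respond on chemotherapy alone. A log-rank test on responders then mixes two things: any effect on how long a response lasts, and the difference in who responded. Stratifying by ECOG PS, brain metastases and liver metastases removes only what those three baseline factors explain.

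At stake is a secondary claim. A DOR result below 0.05 could be reported as longer response caused by treatment, or a real lengthening could be understated, and the P value would not tell the reader which.

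**Working it through.** **Inputs from the Protocol.** Section 4.1.4: "738 subjects will be finally enrolled in this trial and be randomly assigned (1:1:1) to three groups", so 738 / 3 = 246 per arm. Table S1 (investigator review, RECIST 1.1): responders 188 of 246, 187 of 245 and 145 of 247. The Protocol gives no sample size, power or effect size for DOR.

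**Step 1. Reproduce the stated response rates.** With exact binomial intervals:

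| Arm | Responders | Rate | 95% CI |
|---|---|---|---|
| 1 | 188/246 | 76.4% | 70.6 to 81.6 |
| 2 | 187/245 | 76.3% | 70.5 to 81.5 |
| Control | 145/247 | 58.7% | 52.3 to 64.9 |

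These match Table S1. An unstratified chi-square against control gives P = 0.000027 (arm 1) and 0.000030 (arm 2), in line with the reported P < 0.0001 from the stratified test.

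**Step 2. Size of the imbalance.** Arm 1 exceeds control by 76.4 − 58.7 = 17.7 points. As a share of arm 1 responders this is 17.7 / 76.4 = 23%. In patients, 188 − 145 × 246/247 = 43.6, about 44. To call these 44 the extra responders is to assume that every control responder would also have responded in arm 1.

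**Step 3. Effect on the comparison. Assumptions that are not in the documents:** exponential durations, control median 4 months, extra responders with a median m of 2 to 4 months, and uniform censoring at 6 to 18 months. At the start of response, the arm 1 to control hazard ratio is

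0.768 × HR + 0.232 × (4 / m).

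- HR = 1.0, m = 2: 0.768 + 0.464 = 1.23.
- HR = 1.0, m = 4: 0.768 + 0.232 = 1.00.
- HR = 0.60, m = 2: 0.461 + 0.464 = 0.92.
- HR = 0.60, m = 4: 0.461 + 0.232 = 0.69.

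When the extra responders have the shorter durations they leave the risk set early, so the ratio averaged over follow-up is lower than these starting values. Simulation with 188 and 145 responders gives:

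| True HR in patients who respond on either arm | Extra responders' median | Apparent HR | P < 0.05 (unstratified log-rank) |
|---|---|---|---|
| 0.60 | 2 months | about 0.76 | about 59%, all favouring arm 1 |
| 0.60 | 4 months | about 0.67 | about 88%, all favouring arm 1 |
| 1.0 | 2 months | about 1.15 | about 20% to 22%, nearly all against arm 1 |
| 1.0 | 3 months | about 1.07 | about 8% to 9% |
| 1.0 | 4 months | about 1.00 | about 5% |

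The spread of 20% to 22% is between separate runs.

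**Step 4. A second model.** Treatment raises the response rate as in Table S1 but changes no patient's duration. Durations have an assumed median of 5 months with an 18-month cut-off, and responsiveness is correlated with duration.

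| Correlation | Rejection at nominal 5% | Mean apparent HR |
|---|---|---|
| 0 | 4.7% | 1.00 |
| 0.3 | 8.5% | 1.07 |
| 0.5 | 17.5% | 1.13 |
| 0.7 | 34.9% | 1.20 |

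In both models the test holds its level only when the extra responders' durations resemble those of control responders.

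**The case against.** **DOR exists only for responders, and the plan says so openly.** This stands. Restricting the description to responders is normal, and for that reason the intention-to-treat sentence in section 13.1 is not a real contradiction. The problem is the inferential test placed on that subset.

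**The consequence is small.** This also stands. DOR lies outside the fixed sequence of section 13.2.2 (1). It does not enter the sample size, the interim rules or any stopping decision, and ORR, PFS and OS are compared in all randomised patients.

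**The unequal responder numbers are results, not plan.** Correct. They serve here only to give a size. The objection rests on the design: treatment can change response, and the plan itself tests ORR between arms.

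**The durations are assumed.** Correct, and at the benign end of the range (extra responders with the control median, no effect on duration) the error vanishes.

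Two stronger readings are tempting, and the material does not support them.

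- A reader might infer that the test would reverse the sign for a drug that truly lengthens response. At a true HR of 0.60 no simulated trial was significant in the wrong direction. The average ratio passes 1.0 only for weak effects with short-lived extra responders: with a 2-month median, a true 0.90 appears as about 1.05, while a true 0.80 stays below 1.0 at about 0.96.
- A reader might infer a spurious benefit. That could arise in principle if the extra responders had longer durations than control responders, but no calculation here shows it. Both models bias against the arm with more responders.

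**Conclusion.** The point holds, at minor severity. The Protocol fixes a between-arm significance test on a group that treatment helps to select, and does not label it descriptive. Its P value has no interpretation as a treatment effect on duration. The same applies to the hazard ratio in Figure S2, which section 13.4.2 did not plan.

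Under the stated assumptions, the size is attenuation of a true 0.60 to about 0.76 to 0.67, and false rejection of up to about 22% where duration is unaffected, falling to the nominal 5% when extra responders resemble control responders. These figures illustrate scale and do not estimate the bias in this trial, whose direction is unknown. The PFS and OS conclusions do not depend on any of this.

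**What to change.** In section 13.4.2, keep the Kaplan-Meier curve per arm in responders, with the median and its 95% confidence interval, and state that it is descriptive. Remove the between-arm log-rank P value, and report no DOR hazard ratio as a treatment effect. Exempt DOR from the 0.05 rule in section 13.2.2 (3). Title the display as responders within the intention-to-treat set.

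If a comparison is wanted to serve the secondary objective in section 2, compare mean time in response up to a fixed, pre-stated horizon in all randomised patients, counting non-responders as zero. This uses about 246 patients per arm and keeps the randomised comparison. It answers a different question, because it combines how often patients respond with how long the response lasts, and the text should say so.

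The cost is a wording change and minor programming on data already collected. The downside is that one secondary P value is dropped or replaced.

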#### **3.2.2 Handling of Participant Withdrawals**

Investigators should clearly collect the reason and time of withdrawal, conduct corresponding observation and evaluation of the withdrawn subjects, complete the evaluation content when withdrawing from the study as specified in the study plan, fill in the corresponding original records, and describe the reasons for withdrawal. Subjects who discontinue the study should continue to be

followed for AEs. If possible, these subjects should continue to follow up AEs until it recovers to the baseline level or the investigator believes that follow-up observation is unnecessary.

During the study period, all subjects who received the drug but did not complete the relevant study content of the protocol should have their last examination results transferred to the final result. Subjects who did not follow up as required and evidence of contact should be recorded in the corresponding original records and electronic data collections (EDCs; such as time and date of telephone contact, mailing receipt of registered mail, etc.) and properly preserved.

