#### Secondary endpoints:

- ✓ PFS per RECIST version 1.1 and iRECIST, ORR, DCR, DOR, 6-month PFS rate, 12-month PFS rate, 12-month OS rate, 18-month OS rate, and QOL assessed by investigators.
- ✓ Safety and tolerability based on incidence and severity of AEs and SAEs, as well as abnormal laboratory test indicators.

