#### 4.1 Sample Size Calculation

##### 4.1.1 Method of Sample Size Calculation

There are 3 arms in this study: Intervention arm 1 (TQB2450, Anlotinib, Carboplatin, and Etoposide); Intervention arm 2 (TQB2450 placebo, Anlotinib, Carboplatin, and Etoposide); Control arm (TQB2450 placebo, Anlotinib placebo, Carboplatin, and Etoposide). The primary efficacy endpoints of this trial are PFS and OS. In this study, a fixed-sequence test will be used for comparisons between treatment groups.

The safety analysis and re-estimation of sample size will be conducted by the Independent Data Monitoring Committee (iDMC). The re-estimation of sample size based on PFS is planned after 50% of the planned PFS events (174 cases). At the same time, a safety analysis will be performed. The interim analysis will be conducted by iDMC. One interim analysis for OS is planned for this study after 70% of the planned OS events. If expected efficacy is observed, early declaration of the study due to efficacy would be considered. The interim analysis will be conducted by iDMC.

The previous study showed that the median OS and PFS in the control arm were 10 and 4 months, respectively [5]. Patients were enrolled within a 12-month accrual period with an 18-month follow-up and were randomly assigned (1:1:1) to three groups. The power was 85% with a type I error rate of 0.050 and a dropout incidence of 10%. The type I error rate in the interim analysis for PFS will be controlled by the Method Based on the Sum of P-values (MSP). The initial sample size in this study will be estimated based on PFS using a computer simulation program.

##### 4.1.2 Sample Size Estimation in the Intervention Arm 1

Assuming that the HR for PFS in the intervention arm 1 compared with the control arm is 0.6, the hazard rate in the intervention arm 1 is 0.1040, and that in the control arm is 0.1733 along with exponential distribution. Approximately 165 PFS events are expected if 174 patients are enrolled. A total of 194 patients are recruited and randomly assigned (1:1) to intervention arm 1 and control arm, considering an approximate dropout incidence of 10%. The interim analysis will be conducted when the planned PFS events are ~83. The final analysis will be performed after ~165 of the planned

PFS events.

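### Landmark PFS and OS rates are estimated by Kaplan-Meier but compared with Fisher's exact test, so with censoring the P value does not belong to the reported estimate

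*Protocol*

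**What the plan says.** Protocol section 13.4.2 gives the same instruction twice: the rates "will be estimated using the Kaplan-Meier method and compared with Fisher's Exact Test". In full, for 6 and 12 months: "The PFS rate and the corresponding 95%CI for each intervention arm will be estimated using the Kaplan-Meier method and compared with Fisher's Exact Test". For 12 and 18 months: "The OS rate and the corresponding 95%CI for each intervention arm will be estimated using the Kaplan-Meier method and compared with Fisher's Exact Test".

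Section 3.6 lists all four rates as secondary endpoints: "6-month PFS rate, 12-month PFS rate, 12-month OS rate, 18-month OS rate, and QOL assessed by investigators". The end of section 13.2.2 sets a two-sided 0.05 level that "will be used for secondary efficacy endpoints and safety analysis", so the comparisons are meant to be read as tests.

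Nothing else in the protocol names another test for these rates or says how a patient censored before the landmark enters the two-by-two table.

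**The concern.** Fisher's exact test works on counts of patients with and without the event. A patient who is event-free but followed for only nine months has no 12-month status. The table can be completed in three ways:

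- leave such patients out;
- assign them a status, event-free or event;
- multiply the Kaplan-Meier rate by N and treat the product as an observed count.

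The first two test a crude proportion that is not the Kaplan-Meier rate. The third uses the right rate but treats every patient as fully observed, so its variance is too small. In each case the estimate and interval come from one method and the P value from another.

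Censoring before a landmark is part of the design. Section 4.1.1 plans 10% dropout, and section 4.2 puts the final PFS analysis and the OS interim on one date, when late-enrolled patients have short follow-up. At stake is the reading of four secondary P values.

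**Working it through.** **Inputs.** From section 4.1.1: "Patients were enrolled within a 12-month accrual period with an 18-month follow-up and were randomly assigned (1:1:1) to three groups"; control medians of 10 months (OS) and 4 months (PFS). From 4.1.2 and 4.1.3: hazard ratios for OS of 0.7 and 0.72, and for PFS of 0.6 and 0.65. From 4.1.4: 738 patients (246 per arm), and 348 and 497 deaths at the OS interim and final. Assumed: uniform accrual, exponential survival and, in steps 2 to 5, administrative censoring only.

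**1. The plan's own figures.** Section 13.4.2 gives none to reproduce, so the design inputs were checked.
- For OS, arm 1 against control: 4(1.960 + 1.036)² / (ln 0.7)² ≈ 283 events; the plan states 284.
- The exponential model gives 283.6 events from 381 patients at 30 months.
- 381/0.9 rounds up to 424, and 0.7 × 497 = 347.9, both as stated.

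**2. Date of the cuts.** Expected events by month T are 246 × Σ[1 − (e^(−λ(T−12)) − e^(−λT))/(12λ)] over the three arms.
- With λ = 0.0693 for control OS, times 0.7 and 0.72 for the other arms, 348 deaths fall at month 17.85 (134.6 + 105.6 + 107.8) and 497 at month 26.66.
- The same formula for PFS gives about 554 events at month 17.85, beyond the 347 required, so the death count sets the joint date.

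**3. Follow-up at month 17.85.** Potential follow-up runs from 5.85 to 17.85 months.
- Under 12 months: (12 − 5.85)/12 = 51% of patients.
- Under 6 months: 0.15/12, about 1%.
- None has 18 months.

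**4. What a 12-month table would contain, control arm.** The share known event-free is (5.85/12) × S(12). The share censored event-free is (S(5.85) − S(12))/(12λ).
- OS: 0.4875 × 0.435 = 0.212 known; (0.667 − 0.435)/0.832 = 0.278 censored.
- PFS: 0.4875 × 0.125 = 0.061 known; (0.363 − 0.125)/2.079 = 0.114 censored.

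| Proportion event-free at 12 months | OS | PFS |
|---|---|---|
| True rate, targeted by Kaplan-Meier | 43.5% | 12.5% |
| Censored counted as event-free | 49.0% | 17.5% |
| Censored left out | 29.4% (0.212/0.722) | 6.9% (0.061/0.886) |
| Censored counted as events | 21.2% | 6.1% |

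**5. Rate times N as counts.** The ratio of Greenwood to binomial variance at month 17.85 is 1.27 (control) and 1.25 (arm 1) for 12-month OS, and 1.37 and 1.30 for 12-month PFS. The understatement is 1 − 1/ratio: 1 − 1/1.25 = 20% up to 1 − 1/1.37 = 27%. Simulated two-sided type I error of Fisher's test on these counts, 246 per arm, 10,000 runs:
- 12-month OS: 6.5% (control hazard) and 6.9% (arm 1 hazard);
- 12-month PFS: 7.8% and 6.9%;
- 18-month OS at month 26.66 (variance ratio 1.05): 4.65%;
- 6-month PFS: 4.1%.

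**6. With dropout added** (assumed 10% per 12 months; 4,000 runs per scenario).
- 12-month OS at month 18: 31-34% are censored before the landmark. Power at hazard ratio 0.7 is 0.67, 0.54 or 0.28 with censored patients as event-free, left out or as events, against 0.65 for the Kaplan-Meier comparison. Rate times N gives 7.5% type I error.
- 18-month OS at month 30: 8-9% are censored. Power is 0.77, 0.80 or 0.72, against 0.81. Type I error for Fisher's test is 3.7-4.6%.
- 18-month OS at month 30 with unequal dropout (assumed 15% against 5% per 12 months): type I error is 15.5%, 7.5% or 16.2%, against 5.7%.

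A Z test on the complementary log-log Kaplan-Meier rates with Greenwood variance kept type I error between 4.7% and 5.7% in every null scenario of this step, including those for PFS.

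**The case against.** The strongest defence is that little depends on these P values. The four rates lie outside the fixed sequence of section 13.2.2, and the same curves are compared by stratified log-rank test with Cox hazard ratios. With equal censoring, counting censored patients as event-free does not inflate the error: simulated type I error at the early cut is 3.8-4.4%. The inflated figures need either pseudo-counts, which the protocol does not prescribe, or unequal dropout, which it does not state. Nor does it say that the OS landmark rates will be tested at the OS interim. The handling of censored patients could also be left to an analysis plan that is not shown.

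Most of this stands and limits the size of the point. It does not remove it. The protocol names the test, so this is a stated method and not an omitted detail. No rule for filling the table makes Fisher's test a test of the Kaplan-Meier rates. The 12-month PFS rates belong naturally to the final PFS analysis, which is tied to the early cut.

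Stronger readings that a reader might infer are not supported:
- *That the reported rates are wrong.* They and their intervals are Kaplan-Meier estimates. The distorted proportions exist only inside the Fisher table.
- *That section 3.2.2 settles the table.* It says that treated patients who do not complete the study "should have their last examination results transferred to the final result". That sentence concerns examinations after withdrawal. It does not mention survival status or landmark tables, and it does not address patients censored only because the data were cut.
- *That type I error reaches 8-9%.* This follows from 2Φ(−1.96/√ratio), which describes a normal test. Fisher's test is conservative, and the simulated figures are lower.
- *That all four endpoints are materially affected.* At the early cut hardly any patient is censored before 6 months, and at 497 deaths the 18-month OS comparison shows no inflation.

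**Conclusion.** The point holds as a mismatch between estimate and test. The Kaplan-Meier rates and intervals can stand; the Fisher P values do not correspond to them when patients are censored before the landmark.

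Under planned accrual and administrative censoring only, the effect is material for the 12-month rates at about month 17.8. The control proportion moves from 43.5% to 49.0% (OS) and from 12.5% to 17.5% (PFS) if censored patients count as event-free. With pseudo-counts, type I error is about 6.5-8%. It is small for 6-month PFS, for 18-month OS at 497 deaths, and under light balanced censoring. It can be larger if dropout differs between arms, which is an assumption here.

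These sizes rest on uniform accrual, exponential survival, the planned hazard ratios and, for 12-month OS, on the rate being tested at the interim cut. Severity is low to moderate: secondary P values only, with no effect on the primary log-rank tests.

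**What to change.** In section 13.4.2, replace Fisher's exact test for the four landmark rates with a Z test on the Kaplan-Meier estimates using Greenwood variance, for example on the complementary log-log scale. Report the difference in rates with its 95% CI. State at which data cut each landmark is tested.

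The cost is a wording change and one procedure call. The estimates and variances are already needed for the planned intervals, and sample size, data collection and the fixed sequence do not change.
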